## Abstract

Women are exposed to increased burden of mental disorders during the perinatal period: 13–19% experience postpartum depression. Perinatal psychological suffering affects early mother-child relationship, impacting child’s emotional and cognitive development. Return-to-work brings additional vulnerability given the required balance between parenting and job demands. The MAternal Mental Health in the WORKplace (MAMH@WORK) project aims to develop and evaluate the effectiveness of a brief and sustainable intervention, promoting (a) maternal mental health throughout pregnancy and first 12 months after delivery, and (b) quality of mother–child interactions, child emotional self-regulation, and cognitive self-control, while (c) reducing perinatal absenteeism and presenteeism. MAMH@WORK is a three-arm randomized controlled trial. A short-term cognitive-behavioral therapy-based (CBT-based) psychoeducation plus biofeedback intervention will be implemented by psychiatrists and psychologists, following a standardized procedure manual developed after consensus (Delphi method). Participants (*n* = 225, primiparous, singleton pregnant women at 28–30 weeks gestational age, aged 18–40 years, employed) will be randomly allocated to arms: CBT-based psychoeducation intervention (including mindfulness); psychoeducation plus biofeedback intervention; and control. Assessments will take place before and after delivery. Main outcomes (and main tools): mental health literacy (MHLS), psychological wellbeing (HADS, EPDS, KBS, CD-RISC, BRIEF COPE), quality of mother–child interaction, child–mother attachment, child emotional self-regulation and cognitive self-control (including PBQ, Strange Situation Procedure, QDIBRB, SGS-II, CARE-Index), job engagement (UWES), and presenteeism. Intention-to-treat and per-protocol analyses will be conducted; Cohen’s d coefficient, Cramer’s V and odds ratio will be used to assess the effect size of the intervention. MAMH@WORK is expected to contribute to mental health promotion during the perinatal period and beyond. Its results have the potential to inform health policies regarding work–life balance and maternal mental health and wellbeing promotion in the workplace.

## 1. Introduction

Pregnancy and childbirth are transition events that encompass major physiological, physical and psychological changes in a woman’s life. Although it is usually considered a pleasant life stage, the perinatal period (i.e., the period encompassing pregnancy and one year after childbirth; [1]) is often very challenging and requires continuous psychosocial adjustment of the parents-to-be [2], in particular of the mother, who becomes more vulnerable and likely to develop mental disorders [3,4]. Throughout pregnancy, women often experience psychological distress related to rapid changes in body size and shape to which they must adapt, and this can be a potential trigger for body dissatisfaction [5,6]. Such physical changes become intertwined with those at the psychological level. Parents-to-be frequently experience ambivalence during the first trimester of pregnancy, a period during which they adjust themselves to the prospect of parenthood [7]. This effect is more common in women and precedes the mother’s imaginings of her baby and the production of her own representation of the child (the “imaginary baby”). Childbirth poses a challenge to this antenatal representation, requiring that the mother adjusts to the “real baby” [8].

In the first few days after childbirth, approximately 50% of recent mothers are likely to experience postpartum blues [3], which is mainly characterized by transient mild mood disturbance and tearfulness [4,9]. Postpartum blues symptomatology tends to disappear within approximately ten days after childbirth and no medical intervention is usually required [4]. Despite being a common non-pathological condition, postpartum blues has been associated to the onset of postpartum depression (PPD) [3,10,11]. PPD is the most common mental disorder diagnosed among women during the perinatal period [1,12], with an estimated prevalence of 13–19% [13]. PPD symptomatology is indistinguishable from any other non-psychotic major depression episode at a different stage in a woman’s life, the only difference being the onset, as acknowledged in DSM-5 [14]. Depressed parturients experience depressed mood most of the day or loss of interest and pleasure in usual activities, in combination with at least four of the following symptoms: significant weight loss or weight gain, insomnia or hypersomnia, psychomotor agitation or retardation, fatigue or loss of energy, feelings of worthlessness or excessive guilt, diminished ability to think or concentrate, and recurrent thoughts of death or suicide [14]. The onset of PPD is influenced by several factors, such as history of mental disorders [3,4,15], perinatal body dissatisfaction [16], marital satisfaction [17], perceived social support through close relatives and friends [3], life events [15], pregnancy-related complications [15], and hormonal changes [4]. Given the multifactorial nature of PPD and its prevalence and severity, it is crucial to screen for mental disorders during pregnancy and within four weeks of delivery [14].

The short to long-term negative effects of maternal mental disorders on parenting, child physical health, behavior, and cognitive development are well recognized [13,18,19]. Depressed mothers often experience difficulties in establishing affective and protective feelings towards their infant, a process that usually initiates during pregnancy and extends after childbirth [20,21]. Impaired mother–child bonding has been associated with PPD (e.g., [22,23,24,25,26]), with consequences for the emotional and cognitive development of the child that might persist from childhood into adulthood [13]. However, the direction of the association between PPD and impaired bonding should be interpreted cautiously, as poor bonding also occurs among non-depressed mothers [27]. On the other hand, the establishment of a relationship of affection, warmth, trust, and sense of safety from the child towards the mother (i.e., infant–mother attachment) is potentially impaired by PPD. The latter is a relevant predictor of subsequent child externalizing behaviors (e.g., impulsive behavior, hyperactivity, aggression, and delinquency) and poor social outcomes [28].

Available evidence also indicates that maternal mental disorders influence breastfeeding-related outcomes [13], and that mothers suffering from PPD tend to have shorter and earlier ending breastfeeding patterns when compared to non-depressed women [29]. This is of special significance because breastfeeding is one of the earliest postpartum interactions between mother and child, offering a wide range of benefits for both of them [29]. In addition to impaired bonding (characterized by negative affect towards the child and the inability to adequately respond to their demands), mothers with PPD are also less likely to engage in health-related behaviors. Negligent behavior in regard to sleeping practices, as well as increased odds for child abuse have been identified in a literature review addressing the impact of PPD in parenting [13]. All these factors have consequences for the health and wellbeing of the child (e.g., [18,30]).

Children of mothers with persistent depression are at increased risk for behavioral and developmental negative outcomes (e.g., [31,32]). Stein and colleagues have reviewed epidemiological evidence on the effects of disruptive mother–child relationships in children and adolescents in the context of perinatal mental disorders [33]. They found long-term effects of the exposure to perinatal maternal mental disorders on the behavioral competence and cognitive development of these children. For example, exposure to PPD has been described as a relevant predictor of externalizing behaviors, such as inattention and hyperactivity during childhood (e.g., [34,35,36]). As for cognitive development, data from the Avon Longitudinal Study of Parents and Children, United Kingdom, reveals that adolescents of postpartum depressed mothers were 1.5 times more likely to fail mathematics at age 16; ca. 16% of this association was explained by attentional control [37]. Similar results were obtained for receptive vocabulary and inattention for children aged 4 to 5 years that were enrolled in the Canadian National Longitudinal Survey of Children and Youth [38]. Children from postpartum depressed mothers were 1.94 times more likely to display low receptive vocabulary and increased inattention. It should be noted that the association between perinatal maternal mental disorders and offspring negative outcomes is mediated by several factors [33]. For example, after controlling for family background covariates, the effect reported by Letourneau and colleagues on receptive vocabulary was no longer significant [38].

### 1.1. Return to Work after Childbirth

Maternal mental disorders impair the life of a woman as a whole, including her functioning in the workplace [13,39]. Healthy and motivated employees are fundamental at the organizational level and for the socioeconomic wellbeing of any country [40]. Engaged employees are less likely to experience absenteeism or presenteeism, thus contributing to increased productivity [41]. In addition to individual (e.g., health conditions, and resiliency) and family (e.g., spouse support, and financial strain) characteristics, the workplace in all its dimensions (i.e., interpersonal relations and group dynamics, organizational culture, productivity and quality/safety-related challenges, and external environment) represents a potentially major stress factor to employees [42].

During the postpartum period, many women return to paid work. Maternity leave in Portugal is of 42 mandatory days after childbirth. Portuguese parents are also eligible for 120 or 150 days of paid leave at 100% and 80%, respectively. The specificities of maternal and parental leave vary across the European Union-28. For example, German mothers are eligible for up to 42 non-mandatory days during the antenatal period and paid postpartum leaves of 56 mandatory days. In Sweden, parental leave is up to 240 days of paid plus unpaid leave until 18 months postpartum [43]. These differences in national legislation imply that, depending on the country, European women return to work at different stages of physical and psychological postpartum recovery.

Despite latent psychosocial benefits from being employed [44] and empirical evidence that women respond positively to returning to work after childbirth, recent mothers may perceive this moment as a stressful event [45]. In a qualitative study addressing the perceptions of recent mothers when returning to work within one year after childbirth, several resilience-related challenges were identified, the most common one being role conflict (i.e., the difficulty in balancing work and childcare responsibilities) [45]. This arises from three major forms of conflict between roles: time, strain- and behavior-based conflict [46]. For example, a full-time non-flexible work schedule reduces mother’s time with her child, whereas low levels of social support by either her co-workers or partner can result in conflict between work and childcare responsibilities.

Having a child can interfere with career prosecution, and this can represent a discouraging factor to motherhood. Indeed, women in developed countries are having their first child at an older age. In 2018, Portuguese women were giving birth to their first child at age 30.4 vs. 25.0 back in 1960 [47]. Under this scenario, organizational support is fundamental, and the path to a healthy workplace does require the commitment of organizational leaders [48,49]. The continuous motivation and engagement of all employees implies that leaders adopt an empathic mindset towards the different life and career phases of employees. Towards this end, the European Commission has recently approved a new directive on work–life balance for parents and carers—Directive EU 2019/1158 [50]. With regards to parenting, Directive EU 2019/1158 encourages a gender-balanced use of family-related leaves and flexible working arrangements, thus increasing women’s participation in the labour market (by reducing role conflict).

Maternal mental disorders during the perinatal period and beyond represent an issue of clear societal significance. This strongly argues for interventions targeting the prevention rather than the treatment of such conditions. Available evidence indicates that recent mothers who go through psychological and psychoeducational interventions are at a lower risk of developing PPD when compared to women who receive care-as-usual from their health units [39,51,52,53]. As previously mentioned, multiple factors are involved in the onset of PPD, which implies that identifying the most effective intervention type is difficult and context-dependent [51]. Thus, it is not surprising that both individually-based interventions, including home-visiting interventions, and group interventions have proven effective in reducing PPD, either applied during pregnancy or postpartum [39,53]. In addition, interventions making use of wearable devices providing biofeedback have also been implemented. In these cases, physiological signals known to vary under stressful situations [54] are monitored through sensors. The processing of these signals provides information regarding the individual’s physiological activity, which in turn allows her/him to respond accordingly [55]. For example, biofeedback on heart rate variability has been proven effective in reducing depression symptomatology during the perinatal period, as measured by Edinburgh Postnatal Depression Scale scores [56,57].

More recently, mindfulness-based therapy (MBT) interventions have also been implemented to reduce perinatal maternal depression, anxiety and perceived stress [58,59]. Mindfulness refers to the non-judgmental experiencing of everyday life [60], and available evidence shows that MBT may reduce anxiety and depression in clinical populations [61,62]. The few studies that assessed the effectiveness of MBT on perinatal mental health outcomes suggest a reduction in anxiety [58,59] and depression symptoms [63]. To the best of our knowledge, no study combining psychoeducational interventions, including short training sessions of mindfulness as a stress coping mechanism, with biofeedback-coupled monitoring of physiological signals have been implemented in pregnant and postpartum women. This is a promising approach, since it combines cognitive, behavioral, emotional, and physiological dimensions, and these are all known to be involved in depression and anxiety phenomena.

The MAternal Mental Health in the WORKplace (MAMH@WORK) project assumes an integrated approach to the promotion of perinatal maternal mental health and is based on three key aspects. First, maternal mental disorders do not only affect mothers—it affects the physical and mental health and wellbeing of her partner and closest family [13,18,19]. Second, possible negative effects for the child (i.e., externalizing behaviors and cognitive development) may go beyond the perinatal period and extend throughout adolescence and into adulthood [33]. Third, work–life balance strategies are essential to reduce the distress associated with the return to work [45] and to promote wellbeing [64]. To tackle these issues, the MAMH@WORK project proposes to develop, implement and assess the effectiveness of an intervention directed at perinatal mental health promotion. This project will combine e-mental health tools and face-to-face intervention methods to promote maternal mental health starting from late pregnancy until one year after childbirth, including the return to work.

### 1.2. Aims and Objectives

The main aims of MAMH@WORK are: (a) to promote perinatal mental health, from the last trimester of pregnancy up to the first 12 months after childbirth, (b) to foster the healthy psychosocial and emotional development of children via an improved quality of early mother–child interactions, and (c) to reduce sickness absence and presenteeism of working-age women during this period. Considering these aims, the main goals of this project are to develop a maternal mental health and wellbeing promotion program and to evaluate its effectiveness. To achieve these goals, it is proposed the design, implementation and effectiveness assessment of a brief group cognitive-behavioral therapy-based (CBT-based) psychoeducation, including mindfulness e-training, combined with biofeedback. Specific objectives are to (a) design an intervention program to promote wellbeing and prevent perinatal mental disorders in Portuguese pregnant women; (b) develop a smartphone app that will provide women with targeted biofeedback based on the continuous (wearable-based) biomonitoring of selected physiological signals; and (c) assess the impact of the intervention on maternal perinatal mental health outcomes, on the interaction between mother and child (namely regarding the quality of mother–child interaction, child–mother attachment and child emotional self-regulation and cognitive self-control), and on the reduction of women’s absenteeism and presenteeism after childbirth.

## 2. Materials and Methods

### 2.1. Study Design and Setting

This is an open-label, three-arm randomized controlled trial of pregnant women who will be followed throughout pregnancy (starting at 28–30 weeks of pregnancy) until 12 months postpartum. The MAMH@WORK project will be conducted at the Environmental Health Institute of Lisbon School of Medicine (ISAMB-FMUL), Portugal, with clinical data being collected at three primary health care units, three hospitals and in a network of private clinics (all part of the MAMH@WORK consortium).

### 2.2. Sampling Details and Characteristics of the Sample

The target population of this mental health promotion project are pregnant women living in Portugal, with no diagnosis of depression, and employed at the time of recruitment. Women will be recruited at 28–30 weeks of gestational age, since antenatal depression is a relevant predictor for PPD [65,66]; thus, the potential effectiveness of the intervention should increase if it starts during pregnancy. All women booked for delivery at Portuguese hospitals attend various antenatal routine appointments in primary and secondary health care units, which are intended to reduce complications during pregnancy and to improve the chances of positive pregnancy outcomes. These appointments also serve for counselling about health behaviors during the antenatal and postpartum periods. Recruitment will take place in the Lisbon Metropolitan Area from three primary health care units and a network of private clinics. Women at 28–30 weeks of gestation attending an antenatal routine appointment will be invited, by their doctors or nurses, to participate with their babies in the study according to inclusion and exclusion criteria detailed below. In case of agreement, women will be asked to sign a data agreement form and will later receive a formal invitation addressed by the research team. To assess their eligibility to be enrolled in the study, women will be presented with a screening questionnaire conducted by trained psychiatrists and psychologists. In addition, clinical inclusion and exclusion criteria, namely serious mental disorders diagnosed, will be evaluated by antenatal healthcare professionals (i.e., general practitioners, obstetricians, psychiatrists, and psychologists).

To be enrolled in the study, women must meet the following inclusion criteria: native Portuguese speakers or women living in Portugal for at least 5 years; intended pregnancy; primiparous, singleton pregnant women at gestational age of 28–30 weeks; aged 18–40 years; employed; eligible for maternal leave; with access to a smartphone; and have had understood and signed the project’s informed consent form.

Exclusion criteria at the baseline are: diagnosis of (a) a serious mental disorder (e.g., schizophrenia, schizoaffective disorder, other psychotic disorders, bipolar and related disorders, and personality disorders), (b) a chronic disease resulting in functional impairment, or (c) a neurodevelopmental disorder (e.g., autism spectrum disorders and intellectual disability); history of major depression; being under antidepressant medication; alcohol and/or drug addiction; high-risk pregnancy; and fetal malformations. These criteria were defined to ensure that relevant stress-related heterogeneity at the baseline will be reduced in the study. In addition to these exclusion criteria, mother–child dyads will be excluded from the study (after enrolment) in case of preterm birth (less than 37 weeks of gestational age), very-low weight at birth (less than 1500 g), or unexpected newborn malformations.

Randomization will follow the minimization procedure [67] aiming for a balanced sample size for educational level and age groups at the baseline (18–24 years old, 25–34 years old, and 35–40 years old). Random numbers and their assignment will be sealed in envelopes, kept in sequence and opened consecutively by trained researchers as pregnant women are screened for eligibility and enrolled in the study.

The minimum sample size for MAMH@WORK project will be 159, that is 53 women in each group. Attrition rate is considered to be approximately 40% and thus, a total of 225 pregnant women, 75 in each arm, will be enrolled in the study. These calculations are based on a literature review on psychological interventions for PPD prevention, which found mean depression scores (± standard deviation) of intervention and control groups of 11.00 ± 14.63 and 11.52 ± 14.93, respectively, at the final assessment of the study [39]. These sample size calculations assume the average difference between intervention and control arms reported by Dennis and Dowswell [39], considering a 95% confidence interval and a 80% power of the test to detect a difference between depression scores of both arms. This sample size allows for a medium effect size of the intervention to be detected for depression and anxiety scores.

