Life events with potential confounding effects at the time of effectiveness assessment include becoming unemployed, diagnosis of cancer and life-limiting illnesses, newborn death, complications during delivery that severely impair mother and/or child, gestational diabetes, preeclampsia and eclampsia diagnosis, as well as losing the spouse, either by getting divorced or after death. See Statistical Analyses subsection for further details on how these will be handled.

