### 2.5. Statistical Analyses

Statistical analyses will be performed using IBM/SPSS 26.0 (or a more recent version at the time of data analysis) (IBM Corporation, NY, USA) [70] and R Software (R Foundation for Statistical Computing, Vienna, Austria) [71]. For all statistical analyses, the significance level will be set to α = 0.05.

Two strategies for data analysis will be performed: intention-to-treat (ITT) and per-protocol (PP) analyses. ITT considers all participants allocated to arms at the baseline, thus providing a more conservative estimate of the treatment effect, allowing for noncompliance and protocol deviations. In this case, the last observation carried forward method will be used to deal with missing data. PP analysis includes the subset of participants who completed all evaluations. Results from both types of analyses will be reported when comparing control and intervention groups. For effect size estimation, only PP results will be used, since these allow the identification of the treatment effect under optimal conditions, i.e., without major deviations from the protocol. Sensitivity analyses will be carried out to identify potential effects of data strata and missing data on the outcome.

Univariate description of sociodemographic and outcome variables will be performed by providing central tendency (mean and median) and dispersion (standard deviation and range) measures for each moment of data collection. Normality tests (Kolmogorov–Smirnov test or Shapiro–Wilk test) in combination with kurtosis and symmetry analyses will be used to assess the distribution of the variables under study. Levene´s test will be used to assess homoscedasticity. Baseline between-groups comparisons, i.e., control versus intervention groups, will be tested through ANOVA or its non-parametric equivalent (Kruskal–Wallis) for continuous variables, and chi-square test for categorical variables. Mixed model repeated measure (MMRM) analyses will be used for the analyses of main and secondary outcomes, comparing between control and intervention groups and adjusting for relevant covariates (including potential confounding factors). Mediation and moderation analyses will be explored using structural equation modelling. Conceptually and statistically relevant variables will be selected to adjust the models. The size of the intervention effect will be assessed by calculating Cohen’s *d* coefficient [98] Cramer’s V, and odds ratio.

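### Mother–child dyads are removed after randomisation for birth outcomes, which contradicts the stated ITT set; separately, the text implies adjustment for later life events that may be mediators

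*Protocol article*

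**What the plan says.** **Allocation.** Section 2.2 recruits at 28–30 weeks. The allocation envelopes are "opened consecutively by trained researchers as pregnant women are screened for eligibility and enrolled in the study". Allocation therefore precedes any birth outcome.

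**Removal.** The same section, after the baseline exclusion criteria, adds that mother–child "dyads will be excluded from the study (after enrolment) in case of preterm birth" (below 37 weeks), birth weight under 1500 g or a malformation not foreseen before birth.

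**Analysis sets.** Section 2.5 states: "ITT considers all participants allocated to arms at the baseline". For missing values in this set, "the last observation carried forward method will be used to deal with missing data". The other set is separate: "PP analysis includes the subset of participants who completed all evaluations". Effect sizes are to be taken from that second set only.

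**Life events.** Section 2.3 says: "Life events with potential confounding effects at the time of effectiveness assessment include becoming unemployed". It goes on to name cancer or life-limiting illness, death of the newborn, severe delivery complications, gestational diabetes, preeclampsia or eclampsia, and loss of the spouse. It then directs the reader onward: "See Statistical Analyses subsection for further details on how these will be handled". Section 2.5 does not name these events. Its mixed model compares the arms while "adjusting for relevant covariates (including potential confounding factors").

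**The concern.** There are two separate issues.

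First, an ITT set of all allocated women cannot coexist with a rule that takes some of them out of the study for something that happens after allocation. The Introduction lists complications of pregnancy among the factors that influence the onset of postpartum depression, so the women removed may well differ in prognosis from those who stay. At stake are the population that the result describes and, if removals differ between arms, the validity of the comparison. If follow-up stops at removal, the data cannot be recovered at the analysis stage.

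Second, an event that occurs after randomisation cannot confound the randomised comparison, but it may be a consequence of the intervention. The programme addresses coping, work–life balance and return to work, so job loss or separation could lie on the causal path. Adjusting for such an event can remove part of the effect and can open a path through shared causes of the event and the outcome.

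**Working it through.** **1. Exclusion rule against ITT definition**

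| Item | Source | Content |
|---|---|---|
| Time of allocation | Section 2.2 | At enrolment, 28–30 weeks |
| Removal trigger | Section 2.2 | Three findings known only at or after birth |
| What is removed | Section 2.2 | Mother and child together, from the study |
| ITT set | Section 2.5 | Everyone allocated |
| PP set | Section 2.5 | Those who complete every evaluation |

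Nothing limits the removal to child outcomes or to the PP set. The two statements cannot both be carried out.

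**2. Can LOCF restore these women?** Table 1 gives the timing of the EPDS, a main outcome, as postpartum only. The first postpartum visit is at two weeks (Section 2.4). A woman removed at birth has no earlier EPDS value to carry forward and contributes none to the mixed model. The same holds for the other instruments listed as postpartum only, such as the PBQ, UWES and presenteeism questions. An instrument also used in pregnancy would have an earlier value, but it would predate the birth.

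**3. How many women?** The plan's figure is 225 enrolled, 75 per arm. It gives no rate for the three birth outcomes, so there is no figure of its own to reproduce. With p an assumed removal rate, the expected loss is 225 × p:

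| p (assumed) | Of 225 | Per arm (75 × p) |
|---|---|---|
| 2% | 4.5 | 1.5 |
| 5% | 11.25 | 3.75 |
| 8% | 18 | 6 |
| 10% | 22.5 | 7.5 |

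**4. When does removal or adjustment bias the comparison?** This was checked by simulation with 2,000,000 women per scenario and inputs that are all assumed. The direct effect is −0.50 SD. The event worsens the outcome by g SD. A frailty shared by event and outcome has coefficient 0.5 on the outcome and 1 on the log-odds of the event. Expected ITT effect = −0.50 + (p₁ − p₀) × g, where p₀ and p₁ are the event rates under control and intervention. For example, at 8% v 5% with g = 1: −0.50 − 0.03 × 1 = −0.53.

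| Event rate, control v intervention | g | All women | Event cases excluded | Event adjusted for | Shift on exclusion |
|---|---|---|---|---|---|
| 8% v 8% | 0.5 | −0.501 | −0.500 | −0.500 | 0.000 |
| 8% v 8% | 1 | −0.500 | −0.501 | −0.501 | −0.001 |
| 8% v 5% | 0.5 | −0.515 | −0.486 | −0.486 | 0.029 |
| 8% v 5% | 1 | −0.529 | −0.486 | −0.485 | 0.043 |
| 10% v 5% | 1 | −0.549 | −0.478 | −0.477 | 0.071 |
| 20% v 10% | 0.5 | −0.552 | −0.461 | −0.458 | 0.091 |
| 20% v 10% | 1 | −0.599 | −0.458 | −0.456 | 0.141 |

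At 8% v 5% with g = 0.5, the shift of 0.029 splits into 0.03 × 0.5 = 0.015 of effect passing through the event and 0.500 − 0.486 = 0.014 from selection on the shared frailty. With equal rates there is no shift.

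**5. Are the listed life events post-randomisation?** Employment is an inclusion criterion, so becoming unemployed must follow enrolment. Newborn death and delivery complications must too. Loss of the spouse and serious illness as events of follow-up also come later. Gestational diabetes and preeclampsia might precede enrolment in some women. Section 2.3 sends the reader to Section 2.5 for their handling, and the only wording there that fits is the covariate phrase in the mixed model.

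**The case against.** The case on the other side has real weight.

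- **Bias is not shown.** A reader might infer that the exclusion rule does bias the effect. The documents do not support that. They give no event rates and nothing to suggest that two four-hour sessions before delivery alter preterm birth or birth weight. A malformation is present before allocation and only found later. If rates are equal across arms, bias is near zero. This stands, but the contradiction in the text and the change of population remain even with equal removals.
- **Adjustment for life events is inferred.** Section 2.5 never names them. It also plans sensitivity analyses, and mediation and moderation models. Section 2.4 lists life-event data just before further moderators and mediators, so an exploratory use is possible. A full covariate list may properly sit in the SAP. This stands as a limit on confidence: adjustment is the likelier reading, not a stated rule.
- **Adjustment does not contradict the ITT set.** A reader might merge the two issues. Covariates do not change who is analysed, so the contradiction comes from the exclusion rule alone.
- **The trial would adjust away its own target.** This is tempting for a return-to-work study, but the stated work outcomes are absence, presenteeism and engagement. Unemployment is not among them.
- **Losses on top of the 40% attrition allowance.** The article does not say what that allowance covers, so this cannot be asserted. High-risk and multiple pregnancies and known fetal malformations are already excluded at baseline, which may put the removal rate low in the assumed range.

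**Conclusion.** The exclusion rule in Section 2.2 and the ITT definition in Section 2.5 contradict each other as written, and the plan's missing-data method cannot reconcile them for the EPDS. This conclusion needs no assumption. Its consequence is an estimate restricted to women with favourable births. The number affected is unknown: 4.5–22.5 of 225 at an assumed 2–10%. Bias in the comparison is possible, not demonstrated. Under the assumed simulation inputs it is zero with equal event rates, 0.03–0.04 SD at 8% v 5%, 0.07 at 10% v 5% and 0.09–0.14 at 20% v 10%. The last pair is better suited to all life events taken together than to the three birth outcomes.

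The life-event part holds with less certainty. The two sections together imply adjusting for variables that mostly arise after randomisation, some of which may be mediators, and the article offers no other handling.

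The first part should be settled before follow-up begins, because mothers who have been dropped cannot be recovered. The second can be settled at any time before analysis.

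**What to change.** 1. Keep every randomised mother in follow-up and in the ITT analysis of maternal and work outcomes, whatever the birth outcome. Confine the birth-outcome restriction to the child and interaction outcomes, or to sensitivity analyses.
2. Limit the covariates of the main models to variables fixed before randomisation: educational level and age group (the minimisation factors), recruitment setting, and the baseline score where the instrument is measured at baseline. The EPDS has none, since Table 1 lists it as postpartum only.
3. Report later life events by arm, and use them only in sensitivity or exploratory mediation analyses. Section 2.5 already provides for both kinds.
4. Report effect sizes from the ITT set as well. An effect size taken only from women who complete every evaluation would still omit the others, even with the ITT set restored.

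Cost: questionnaire follow-up of a few more mothers, a slightly more heterogeneous sample, and changes of wording in Sections 2.2, 2.3 and 2.5.
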